**1. Study design**

1）Study design: The study is a prospective, randomized, controlled, double-blinded trial.

2）Randomization: Using computer software to generate random sequences, patients were randomly assigned to one of three groups (high-dose, low-dose or control group）based on the grouping of random numbers with a 1:1:1 ratio.

3）Blinding: The participants, responsible anesthesiologists, neurosurgeons, and outcome assessors will all be blinded to the allocation until the completion of the study analysis.

4）Research center: Department of Anesthesiology, Beijing Tiantan Hospital, Capital Medical University.

5）Sample size: 228 cases.

6）Rationality and basis of indications: Currently, clinical studies on TXA are mainly limited to orthopedics, obstetrics, cardiac surgery, trauma, etc., and there are few studies in neurosurgery. However, huge meningioma is prone to massive intraoperative bleeding due to its huge tumor volume, rich blood supply, vascular invasion, and cranial nerve damage caused by the tumor. Previous randomized controlled trials of the effect of TXA on intraoperative blood loss in meningioma found that TXA significantly reduced intraoperative blood loss. However, the study sample size was small, and the tumor locations were highly heterogeneous, so the results of these studies cannot be applied to the population of huge meningioma. The purpose of this study is to investigate the effect of TXA on intraoperative blood loss in meningiomas with a diameter over 5cm. At present, our institution has confirmed the safety of TXA in regard to postoperative seizure in patients undergoing meningioma resection, and the efficacy of TXA needs to be further investigated.

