**4. Study population**

The plan is to consecutively recruit patients undergoing elective huge meningioma resection at Beijing Tiantan Hospital, Capital Medical University from January 2022 to December 2024.

**Inclusion criteria:** Patients undergoing elective resection of huge meningioma, and preoperative imaging computed tomography (CT), or magnetic resonance imaging (MRI) suggested meningioma no less than 5cm in diameter in any of three axes; patients aged between 18 and 65 years; ASA physical status Ⅰ to Ⅲ; get written informed consent.

**Exclusion criteria:** Allergic to TXA; with a history of thrombotic disease; under anticoagulant or antiplatelet therapy; informed consent cannot be obtained.

When a serious adverse event (SAE) occurs during the trial, we will closely monitor the event until it is resolved and stabilized. The SAE would be immediately reported to the relevant authorities, and the principal investigator would be notified to determine the severity and consequence. In case of intraoperative adverse events such as severe allergy to the research drug, the infusion of the research drug would be stopped according to the judgment of the anesthesiologist.

1. **Study method**
2. **Blinding:** Study participants, anesthesiologists, and post-operative outcome assessors will be blinded to randomization. Randomization code will be prepared in opaque envelopes, and randomization will be concealed until the primary outcome assessment of the last patients is accomplished. If there was a life-threatening SAE during the intervention, the principal investigator would decide whether to unblind the case and this participant would be dropped out. TXA and placebo will be prepared by an individual investigator who is blinded to allocation, this investigator will also label the container "research drug". This investigator will not participate in the intervention or any assessment and follow-up.

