**Peri-operation:** Baseline characteristics, family history, medical history, physical examination, preoperative lab test (blood routine, coagulation function and chemistry panel), preliminary radiology diagnosis, pre-operative evaluation (GCS score, Charlson complications score, ASA classificaiton, Karnofsky score, Caprini thrombosis risk score).

**Intraoperative:** 1) target mean arterial pressure; 2) cranial nerve block; 3) use of positive inotropic drugs or vasopressor; 4) average inhaled oxygen concentration; 5) coagulation; 6) arterial blood gas (ABG) test; 7) estimated blood loss; 8) type and volume of allogenic transfusion; 9) intraoperative adverse events; 10) tumor resection extension; 11) surgical hemostasis score and hemostasis difficulty; 12) use of topical hemostatic agents; 13) anesthetic drugs; 14) anesthetic parameters; 15) physiological parameters.

**PACU：**1) time of PACU admission; 2) PACU events; 3) drug use; 4) time of PACU discharge.

**Day 1**: 1) outcomes: assessment time, KPS score, GCS score, postoperative epilepsy, embolism, infection, postoperative hematoma, re-operation, ICU admission, death, other adverse events, and assessment of neurological dysfunction; 2) laboratory test; 3) assessment of thrombosis risk by Caprini score.

**Day 3**: outcomes: assessment time, postoperative epilepsy, embolism, infection, postoperative hematoma, re-operation, ICU admission, death, other adverse events, and assessment of neurological dysfunction.

**Day 5±2**: 1) outcomes: assessment time, death, postoperative epilepsy, embolism, infection, postoperative hematoma, re-operation, ICU admission, other adverse events, and assessment of neurological dysfunction; 2) Brice Awareness Questionnaire 5±2 days after surgery; 3) postoperative brain image and EEG.

**Discharge:** 1) pathology diagnosis; 2) discharge summary (date of discharge, recovery, length of stay, referral, length of stay in ICU, hospital charges, epilepsy medication); 3) postoperative treatment plan; 4) clinical assessment (anemia, epilepsy, embolism, infection, hematoma, re-operation, blood transfusion, etc.).

**180 days**: 1) outcomes: assessment time, death, KPS score, GCS score, postoperative epilepsy, embolism, infection, postoperative hematoma, re-operation, ICU admission, other adverse events, and assessment of neurological dysfunction.

1. **Follow-up period**

**Follow-up period:** the day before surgery, 1, 3, 5±2 and 180 days after surgery.

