**Follow-up items:** examination (blood routine, coagulation function and chemistry panel) on the first day after surgery, Caprini risk score on the first day after surgery, KPS score on postoperative day 1, day 3, day 5 ±2 and at discharge and on 180 days. Others include GCS score and complication evaluation.

1. **Outcome assessments**

The primary outcome is the estimated cumulative intraoperative blood loss, which is calculated using the formula: collected blood volume in the suction canister (mL) – the volume of flushing (mL) + the volume from the gauze tampon (mL).

The secondary outcomes include:

1. Intraoperative coagulation function monitoring assessed by rapid TEG at the beginning and the end of the operation.
2. Calculated blood loss: Calculated blood loss = estimated blood volume×(Hcti−Hctf)+transfused RBC volume]/Hctmean.
3. Intraoperative cell salvage use and allogeneic blood products use. The indications for routine blood transfusion in our institution are as follow:

**a.** Hb < 9g/dl or Hct < 30%. If the intraoperative pathology consultation indicated a WHO classification of II or I, we will first consider cell salvage. If intraoperative pathology was unavailable or WHO classification > II, allogeneic blood transfusion will be preferred.

**b.** Use of frozen plasma, cryoprecipitate, and platelet products, will be initiated based on the American Society of Anesthesiologists Task Force on Blood Component Therapy: PT/APTT is more than 1.5 times prolonged, fibrinogen <1g/L, or diffuse microvascular bleeding at the surgical field (although there is no surgical hemostasis and/or no visible clots in the surgical field).

1. Simpson grading system for the extent of meningioma resection.
2. Hemostasis: Hooda score.
3. Operative field surgical hemostasis score using VAS score.

Safety outcome includes 1) frequency and episodes of postoperative seizure; 2) other intraoperative complications (allergy, hypoxemia, refractory hypotension, pulmonary embolism, etc.) other postoperative complications (venous thrombosis, new cerebral ischemia, intracranial hematoma, hydrocephalus, infection, abnormal renal function, myocardial infarction).

Economic outcome: 1) ICU admission, length of ICU stays; 2) length of hospital stay and hospital charge.

1. **Potential risks, benefits of the project & risk management**

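### The protocol gives two different points for ending the blind, and the earlier one falls before the last patients' postoperative safety assessments.

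*Protocol*

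**What the plan says.** The protocol fixes the end of blinding in two places.

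- **Study design, item 3 (Blinding):** participants, responsible anesthesiologists, neurosurgeons and outcome assessors "will all be blinded to the allocation until the completion of the study analysis".
- **Study method, Blinding:** the code is held in opaque envelopes and "randomization will be concealed until the primary outcome assessment of the last patients is accomplished". The same paragraph says that participants, anesthesiologists and post-operative assessors are blinded. It gives no end point for them, does not list the neurosurgeons, and does not say who may see the code once it is released.

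The timing follows from two other sections. Under Outcome assessments, "The primary outcome is the estimated cumulative intraoperative blood loss", computed from suction, flushing and gauze volumes. Under Follow-up period, visits take place "the day before surgery, 1, 3, 5±2 and 180 days after surgery". The day-180 list under Trial procedures reads "outcomes: assessment time, death, KPS score, GCS score, postoperative epilepsy, embolism, infection, postoperative hematoma, re-operation, ICU admission, other adverse events", and it goes on to neurological dysfunction.

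Two neighbouring statements matter separately. Recruitment runs "from January 2022 to December 2024", and the Study period section gives the same months for the whole study. The Blinding item under Study method also states that "TXA and placebo will be prepared by an individual investigator who is blinded to allocation".

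**The concern.** The primary outcome is complete on the day of surgery, while every postoperative safety outcome comes later. A release rule tied to the primary outcome therefore allows the code to be opened while safety follow-up is still running. Epilepsy and neurological dysfunction depend partly on the assessor's judgement. The section on potential risks names epilepsy as the main adverse event of tranexamic acid, followed by embolic events. If allocation reached the assessors early, the late safety comparison could be biased. The other statement in the protocol would prevent this, but a reader cannot tell which of the two governs.

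**Working it through.** There is no stated figure to reproduce. The check sets the statements side by side and then sizes the exposure.

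**Release points compared**

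| Section | Blind or concealment ends at | Timing for the last patient |
|---|---|---|
| Study design, Blinding | completion of the analysis | after all follow-up, if the analysis includes it |
| Study method, Blinding | primary outcome of the last patient assessed | day 0 (end of surgery) |
| Follow-up period | (last planned visit) | day 180 |

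For the last patient, the earlier release point precedes the assessments on days 1, 3, 5±2 and 180. The gap to the last planned visit is 180 days.

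**Patients with follow-up outstanding when the code may be opened**

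Inputs from the protocol: N = 228; recruitment from 1 January 2022 to 31 December 2024, which is 1096 days. Assumptions: uniform accrual, recruitment to the last day, and the code opened on the day of the last operation.

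Formula: patients still short of day d = N × d / accrual days.

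- Day 180: 228 × 180 / 1096 = 37.4, about 37 patients (16%).
- Day 7, the upper edge of 5±2: 228 × 7 / 1096 = 1.5.
- Day 5: 228 × 5 / 1096 = 1.0.

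Sensitivity of the day-180 figure to the length of accrual, at 30.4375 days per month:

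- 36 months: about 37 (16%).
- 30 months: 228 × 180 / 913.1 = 44.9, about 45 (20%).
- 24 months: 228 × 180 / 730.5 = 56.2, about 56 (25%).

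**Calendar (separate point)**

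- 31 December 2024 + 180 days = 29 June 2025, about six months after the stated study end.
- 31 December 2024 − 180 days = 4 July 2024. Only patients operated on by then can complete the 180-day visit within the stated period.

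**Preparer (separate point)**

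Under Grouping and intervention the arms differ in content: a tranexamic acid bolus plus infusion, a tranexamic acid bolus only, or saline, with weight-based dosing of the active drug. No pre-coded kits or third party are described. A person who makes up the assigned contents would normally know what they are. The same paragraph already keeps this person out of the intervention, assessment and follow-up.

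**The case against.** The two statements can be read together. One concerns people and the other concerns the envelopes, so the code could go to an analyst for the primary analysis while assessors stay blinded. The Study method paragraph supports this reading in part, since it calls the post-operative assessors blinded. A reader might infer that the late seizure, thrombosis and neurological assessments will be made with allocation known. The protocol does not support that: nowhere does it say that assessors receive the code. This part of the objection stands, and it reduces the point from an established bias to a permitted risk. It does not remove the point, because the benign reading is not written down.

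A reader might also infer that the early seizure and thrombosis data are broadly exposed. They are not. Only one or two patients would still be inside the day 5±2 window, and the section on potential risks monitors adverse effects of the drug only through the fifth postoperative day. The outcome list ties no safety outcome specifically to day 180. Death, re-operation and ICU admission, also collected then, leave little room for judgement.

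Finally, the calendar does not aggravate the release problem. If the study really closed in December 2024, the late 180-day visits would not take place at all, so they could not be made unblinded. The two harms are alternatives. The calendar and the preparer wording are issues in their own right and say nothing about when the code opens.

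**Conclusion.** The point holds as an unreconciled difference between two release rules. Followed as written, the Study method rule permits the code to be opened before the last patient's postoperative safety assessments and while about 37 of 228 patients (16%) still lack the day-180 assessment. That figure rests on uniform accrual over 1096 days, recruitment to the end of the window, and opening on the day of the last operation. It rises to 45 or 56 if the same number accrues in 30 or 24 months. It counts patients whose assessment could be exposed, not patients whose assessment would be biased. Bias further requires that the code reach the assessors, which the protocol neither states nor rules out after release. The primary outcome and patients who have completed follow-up are not affected. The risk is confined mainly to the day-180 epilepsy, embolism and neurological data, and it can be removed at little cost.

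**What to change.** Put one rule in both Blinding items: the code stays sealed until the last 180-day assessment is complete and the database is locked, and participants, anesthesiologists, neurosurgeons and outcome assessors stay blinded until then. If the sponsor prefers to keep these people blinded until the analysis is complete, as Study design now says, both items should say so and state which role may use the code for the analysis. Changing only one item would leave the two in disagreement. The cost is wording, plus waiting for follow-up that is already planned.

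Separately:

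- Extend the stated study end to about the end of June 2025, so that the 180-day visits of patients recruited up to December 2024 fall within it. This costs about six months of study time. It would not be needed if the last operation took place by 4 July 2024.
- Reconcile the description of the preparer as blinded with the task of making up arm-specific contents. Either describe that person as unblinded, keeping the existing exclusion from the intervention, assessment and follow-up, or describe the arrangement that keeps the preparer blinded. This is wording only.

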Meningiomas are the most common intracranial tumors, accounting for more than 30%[1]. Although the nature of meningioma is mostly benign, due to its occupying effect and invasion of blood vessels, meningioma patients are often accompanied by severe intracranial pressure elevation, encephaledema, and cranial nerve injury, and thus lead to serious neurological dysfunction. Huge meningiomas, defined as diameter ≥5cm, account for about 11% of primary intracranial neoplasm[2]. surgical resection of huge meningiomas is the preferred treatment to improve neurological outcomes. However, most of the huge meningiomas are accompanied by a rich blood supply, compressing and/or distorting blood vessels in their growth process. Some of the meningiomas also surround peripheral blood vessels and involve the venous sinuses, invading the scalp and skull, and the blood loss during resection could be as high as 4000mL[2]. Besides that, the tissue plasminogen activator in tumor and peritumoral brain tissues can induce fibrinolysis and contribute to intraoperative hemorrhage[3]. Massive intraoperative bleeding and severe hemodynamic fluctuations during the resection of huge meningioma may lead to organ injury, coagulopathy and even be life-threatening[4, 5]. Therefore, perioperative blood management of huge meningioma resection is challenging.

There are many techniques for perioperative blood management in neurosurgery, but each blood management technique is accompanied by certain deficiencies and a heavy economic burden. Even with all of the above blood management methods, allogenic transfusion is inevitable in some cases due to excessive blood loss, while allogenic transfusion presents a high risk of immunosuppression, hemolysis, postoperative infection, and transfusion-related lung injury, resulting in prolonged hospital stay and even death[6-10].

Tranexamic Acid (TXA) is a synthetic antifibrinolytic drug with a lysine-like structure. TXA can inhibit plasminogen activation and prevent plasminogen from binding to fibrin, thus blocking the fibrinolytic process, preventing thrombolysis, reducing bleeding, and reducing the blood transfusion rate[11, 12].

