The audit team will assess the research progress, ensure the investigator and patient follow the protocol, and resolve urgent issues through regular site visits, letters, or phone calls. During these visits, the audit team and the principal investigator will jointly supervise the following key points: informed consent, recruitment and follow-up, and documentation and reporting of SAEs.

1. **Data preservation**

All data will be recorded in the paper CRF, which will be kept in the department's locked filing cabinet for at least 5 years. Both original and nature language data are encoded for data storage, review, tabulation, and analysis. The data will be securely entered and stored in an electronic database. Double data entry will be used.

1. **Data monitoring committee**

The Data Monitoring Committee (DMC) will be composed of experts in anesthesiology, ethics, statistics and methodology, as an independent body to monitor the safety, efficacy, ethical issues, and progress of the trial. The DMC will conduct audits through regular interviews or telephone calls. DMC reserves the right to review recruitment process at any time. The audit process will be independent.

1. **Statistics**

Sample size and statistical power: According to previous research reports, the intraoperative blood loss for huge meningioma was about 1000ml, and the standard deviation of the population was about 400ml. A single TXA infusion effectively reduced the amount of blood loss by about 25%, and continuous TXA infusion further reduced the amount of blood loss by 25%. Therefore, the estimated effect size is 250ml. A sample size of 228 patients (76 per group) is calculated to provide 90% power to detect the between-group difference at a significance level 𝛼 of 0.017 and the overall type I error of 0.05, with a dropout rate of 2.5% with Bonferroni adjustment.

1. Statistical analysis principle: Intention-to-treat analysis.
2. The Student’s t-test will be used to compare the primary outcome between groups, and a p-value <0.017 will be considered as a significant difference between the two groups. The overall p-value<0.05 was considered as a significant difference in blood loss among the three groups.

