**Study protocol Modify Description**

| Modify item/page/line number | Original contents- the protocol for ethics review (V1.1.1) | Modified contents-the protocol manuscript |
| --- | --- | --- |
| Study method-standard anesthesia management/Page10/line10 | Intraoperative anesthesia can be maintained by intravenous anesthesia or combined with intravenous anesthesia, | Anesthesia will be then maintained with combined intravenous anesthesia and inhalational anesthesia. |
| Study method-standard anesthesia management/Page10/line11 | and the intraoperative BIS will be maintained between 40 and 60. | to maintain the BIS value between 40 and 50. |
| Study method-standard anesthesia management/Page10/line26 | H3 receptor blocker (Tropisetron 5mg) will be administered before end of surgery to prevent nausea and vomiting. | Not mentioned. |
| Study method-statistics analysis for primary outcome /page15/line26 | The Student’s t test for primary outcome analysis | Student t test or the Mann-Whitney U test, the multiple linear regression model or two-way analysis of covariance will be applied to account for potential confounders. |
| Study method-statistic analysis for missing data/page15 | Not mentioned | Missing data will be imputed using the worst-case scenarios and last observation carry forward method. |
| Study method-statistic analysis/page4/line14 | Event time data will be analyzed using Kaplan-Meier survival analysis, and differences among groups were assessed using log-rank test and proportional risk regression models. | Not time-to-event analysis. |
| Secondary Outcome assessments/Page19/line20 | Calculated blood loss: Calculated blood loss = estimated blood volume×(Hcti−Hctf)+transfused RBC volume]/Hctmean. | Calculated blood loss is assessed by the formula：  Calculated blood loss (CBL) = estimated blood volume×(Hcti−Hctf)+transfused RBC volume]/Hctmean  Estimated blood volume for women=[weight (kg)^0.425 × height (cm)^0.725 ] × 0.007184 × 2217+age (years) × 106  Estimated blood volume for men =[weight(kg)^0.425 x height (cm)^0.725 ]× 0.007184 x 3,064-825 |
| Intervention/page9/line25 | TXA continuous infusion of 5mg/kg/h until the end of the operation | TXA continuous infusion of 5mg/kg/h until dural closure |

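### Dropping participants after a life-threatening SAE during the intervention conflicts with intention-to-treat and can bias the between-group comparisons in either direction

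*Protocol*

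**What the plan says.** The Blinding paragraph under Study method covers a life-threatening SAE during the intervention: "the principal investigator would decide whether to unblind the case and this participant would be dropped out". The Statistics section then sets the analysis population in one line, "Statistical analysis principle: Intention-to-treat analysis", with no exception for these participants. No other section says that a dropped participant's data are kept and analysed.

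Three other statements bear on the point:

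- **Primary outcome** (Outcome assessments): "The primary outcome is the estimated cumulative intraoperative blood loss". It is measured during the operation in which the trigger can occur.
- **Background**: massive bleeding and haemodynamic fluctuation in this surgery "may lead to organ injury, coagulopathy and even be life-threatening".
- **Safety outcomes** (Outcome assessments): they include "other intraoperative complications (allergy, hypoxemia, refractory hypotension, pulmonary embolism, etc".

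Study population says of an SAE that "we will closely monitor the event until it is resolved and stabilized", and the section on risks requires all adverse events to be recorded.

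**The concern.** Intention-to-treat compares everyone randomised, in the arm to which they were randomised. A rule that removes participants because of an event after randomisation breaks that, and it matters most when the event is related to the outcome. Here it can be. A catastrophic bleed may itself be the life-threatening event, and an intraoperative embolism, allergic reaction or refractory hypotension is a safety outcome in its own right.

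If such events fall unequally across the arms, the comparison is distorted. Removing heavy bleeds from control hides benefit, and removing them from a TXA arm exaggerates it. Removing intraoperative harms from any arm distorts the safety comparison, where one or two rare events among 76 per arm can matter. A participant who leaves the trial in theatre may also contribute nothing at 180 days, and no later analysis can recover data that were not collected.

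The ambiguity adds to this. If only unblinded cases are dropped, removal depends on a discretionary decision that reveals the arm.

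**Working it through.** **1. What the drop-out clause most naturally means.** Stopping the infusion is dealt with separately: in Study population (severe allergy, on the anaesthesiologist's judgement) and in the section on risks (stop and record the cause). The clause must therefore add something. The only other use of the term is the 2.5% dropout rate in the sample size paragraphs, where dropouts are patients lost to the comparison. Removal from the trial is the natural reading, and it conflicts with intention-to-treat.

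**2. The planned sample size, for reference.** Inputs from the sample size paragraph: difference 250 mL, SD 400 mL, alpha 0.017 (taken as two-sided), power 90%, dropout 2.5%.

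- The t-test needs 70.3 per group, so 71; 71/0.975 = 72.8, so 73.
- The Mann-Whitney test, with relative efficiency 3/π = 0.955, needs 70.34/0.955 = 73.7, so 74; 74/0.975 = 75.9, so 76.
- 3 × 76 = 228, as stated.

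The sample size is not at issue. The allowance is 0.025 × 228 = 5.7 patients, or about 2 per group (76 − 2 = 74).

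**3. Effect of dropping heavy bleeds from control.** Assumptions: control mean 1000 mL, n = 76; the number dropped and their blood loss are mine.

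| Dropped from control | Mean of those left | Shift |
|---|---|---|
| 1 at 3000 mL | (76,000 − 3000)/75 = 973.3 | 27 mL |
| 1 at 4000 mL | (76,000 − 4000)/75 = 960.0 | 40 mL |
| 2 at 3000 mL | (76,000 − 6000)/74 = 945.9 | 54 mL |
| 2 largest, normal, SD 400 (simulated) | about 976 | 24 mL |
| 2 largest, lognormal, SD 400 (simulated) | about 967 | 33 mL |

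For the last two rows, the 250 mL difference from low-dose appears as 250 − 24 = 226 mL or 250 − 33 = 217 mL.

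**4. The other direction.** Dropping the two largest bleeds from the low-dose arm (mean 750 mL, SD 400 mL) instead raises the apparent difference to about 273 mL (normal) or 286 mL (lognormal).

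**5. Drops in both arms by threshold.** If half or all losses above 1500 mL led to removal, about 5 to 11% of control and 1.5 to 5% of low-dose would go, and 250 mL would shrink to 196 to 232 mL. With a threshold of 2000 mL it would shrink only to 242 to 247 mL.

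**6. Power** (t-test, two-sided alpha 0.017, 74 per group, SD 400 mL): 92% at 250 mL, 84.5% at 226 mL, 81% at 217 mL. Holding the SD at 400 mL is pessimistic. Trimming the two largest values lowers the control SD to about 375 mL (normal) or 343 mL (lognormal). Averaging variances with 400² gives a pooled SD of √((375² + 400²)/2) = 388 mL or √((343² + 400²)/2) = 373 mL, and power of about 87% in both cases. That is still below the stated 90%, and the bias in the estimate is unaffected.

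**7. Which scenarios fit the planning figures.** The Background says "the blood loss during resection could be as high as 4000mL", so it is tempting to drop two or three controls at 4000 mL. With n = 76 and mean 1000 mL, two such patients force a sample SD of at least √[(2 × 3000² + 74 × 81.1²)/75] = 496 mL. Three force at least √[(3 × 3000² + 73 × 123.3²)/75] = 612 mL. Neither fits an SD of 400 mL, so these cases are left out of the range.

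**The case against.** The best defence is that the clause sits under Blinding, not under analysis, and that the term is undefined. It could mean leaving blinded study treatment, which is compatible with intention-to-treat, and no sentence expressly excludes these participants from analysis. The first part stands as a criticism of the wording. It does not rescue the rule, because stopping the drug is already covered elsewhere and nothing says that the data are kept.

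Four stronger readings might be inferred, and the documents do not support them:

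- **That the heaviest bleeds are removed.** The trigger is a life-threatening SAE, not a blood volume. The named intraoperative complications do not list haemorrhage, and the nearest example in Study population is severe allergy. The Background makes overlap plausible, no more.
- **That serious harms vanish.** SAEs are monitored until stable and all adverse events are recorded. What is unclear is their place in the between-group comparison and whether 180-day follow-up continues.
- **That postoperative seizures are hidden.** The rule applies during the intervention, and the infusion stops by the end of the operation at the latest. Seizures are a postoperative outcome.
- **That imputation causes a large loss of power.** The modification table says "Missing data will be imputed using the worst-case scenarios and last observation carry forward method". It sets no fill value, and blood loss recorded in theatre needs no imputation. Whether that rule suits an outcome measured once is a separate question, on which this point does not depend.

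**Conclusion.** The point holds in limited form. The drop-out rule conflicts with the stated analysis principle on its natural reading, and its scope is ambiguous. That conclusion rests on the text alone and needs no assumed number.

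The size is illustrative. Cases that fit the planned mean and SD move the control mean by about 24 to 54 mL, or 10 to 22% of the 250 mL effect (24/250, 54/250). If few patients are dropped, or the trigger is unrelated to blood loss, the shift is smaller. The direction depends on which arm loses patients, and the documents do not fix that. The 2.5% allowance covers lost numbers, not selective loss.

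The rule should be corrected because it can distort the primary and safety comparisons, may forfeit follow-up that cannot be recovered, and costs almost nothing to change.

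**What to change.** Reconcile the Blinding paragraph with the Statistics section. Delete the drop-out clause and state that an SAE, unblinding or discontinuation of study drug does not remove a randomised participant from the trial. Recorded blood loss is analysed in the randomised arm, and all safety and follow-up data, including day 180, continue to be collected and are analysed in that arm. Participants who withdraw consent are a separate category and should be reported as such.

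The cost is a short amendment. Blood loss and adverse events are already recorded in theatre, and the follow-up visits already exist. No clinical rule, procedure or sample size changes; with all 76 per group analysed, t-test power for 250 mL is about 92%.
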